| To evaluate the implementation of the India ink method as a point of care laboratory diagnosis in selected hospitals, based on the RE-AIM conceptual framework. | Number of services and number of providers that adhered to implementation, age, sex, number of samples tested, test availability, initiation of treatment after positive test. | Frequency (professionals who adhered to the intervention, samples tested, services that adhered to the intervention, age and sex. Chi-square compare frequencies Ex: (relationship between characteristics of professionals and the type of test requested);  Multivariate regression to estimate the “Odds Ratio” (OR) of the relationship between adherence to testing (PS) and the variables: severity of the disease, age of the professional, sex, US, availability of services in the laboratory, and feedback |

# Study limitation

Some limitations were identified, namely:

- The nature of the stepped wedge study, which is long and involves following up participants, poses a risk of losing participants, introducing bias into the analysis of outcomes;

To minimize this fact, all clinicians from the medical service and laboratory technicians from the microbiology sector will be involved in the training and cross-sectional analyses of the outcomes will be carried out.

- Data collection through self-administered questionnaires is likely to be a limitation because participants may respond to please the institution and its managers, and using interviews to collect qualitative data risks participants responding in a way they think is appropriate. the researcher wants to hear;

To minimize this fact, the questionnaires will be anonymous, the researcher will be present when the questionnaire is administered and during the interviews to clarify the interviewee regarding the questions.

# Ethical considerations

The data collected for this study will not contain information that allows the identification of the participants involved, they will be coded and anonymized. Participation will be subject to signing the informed consent form; the link between the code and the participants' names will only be known by the researchers. Confidentiality will be maintained at all times during the research, the data will only be used for this study and never for other purposes.

The study will not change the type of cryptococcosis diagnostic sample in force in the hospitals involved. The study will demonstrate to clinicians and laboratory technicians an alternative for diagnosing cryptococcosis using a non-invasive and easy-to-obtain sample. Patients diagnosed with cryptococcosis will be treated in accordance with current Ministry of Health (MoH) regulations.

The researchers declare that they will comply with good research ethics practices. The study will be submitted to the Boards of Directors of the selected Hospitals and to the Institutional Committee for Bioethics in Health of the Faculty of Medicine/Maputo Central Hospital (CIBS FM & HCM). It will also be reviewed and approved by the National Committee on Bioethics for Health (CNBS).

## Potential risks and how these will be minimized

The study foresees minimal risks for the participants involved in the study, such as discomfort, fatigue, and anxiety. To mitigate risk during training, the importance of ensuring and strengthening information sharing between clinicians and laboratory technicians will be emphasized, and a line of communication will also be provided for study researchers to clarify their doubts, provide support, and resolve issues. your concerns.

## Informed consent

The informed consent process begins with pre-study inclusion, when the study team explains all pertinent information related to the study. Study personnel will explain to each potential participant the nature of the study, its purpose, the procedures involved, the expected duration, the potential risks and benefits involved, and any discomfort that may be associated with participation in the study. See informed consent in the appendix on page 38.

## Confidentiality

The confidentiality of the information collected is extremely fundamental. Research staff will be trained to adhere to, comply with, and follow standards strictly and protect participant confidentiality.

The following measures will be used to protect the confidentiality of the information provided:

- During training, the importance of maintaining confidentiality will be emphasized to the research team;
- Interviews will be conducted in private settings;
- Signed informed consent forms will be filed in a locked file cabinet separately from other study data;
- Participants’ contact details will be stored securely on password-protected computers separately from other study data;
- There will be no registration of names in any data collection terms, therefore, we will use unique identification numbers (IDs) that will be assigned to each participant;
- Unintentionally collected information that is identified in the recordings will be edited;
- Data will be entered directly into a password protected device.
- Data will be regularly uploaded to a secure server.
- Only a limited number of study personnel whose roles require access to identifying information (i.e., signed informed consent form, contact information, master list relating participant names to study ID number) will have access to this type of data;
- Participants will not be identified by their own names in any reports or publications resulting from the research data.

Information will be collected through the REDCap (Research Electronic Data Capture) platform loaded onto the tablet. All copies of data, electronic files including Microsoft Word transcripts and databases will be securely archived at the School of Medicine for a period of five years after the completion of the research..

## Potential benefits

Health professionals will have an opportunity to be trained in the diagnosis of cryptococcosis with a cost-effective technique that uses a non-invasive sample (urine) that is easily obtained. Once trained, healthcare professionals will be able to use this test for laboratory screening of suspected cases of cryptococcosis and treat them based on the etiological diagnosis, not just the clinical (empirical) one.

- 1. Declaration of conflicts of interest

The researchers declare that there is no conflict of interest in the present study, nor monetary benefits resulting from conducting the study.

- 1. Expected results

It is expected that:

- The study provides evidence of the practices and challenges existing in the laboratory diagnosis of Cryptococcosis;
- Health professionals are trained, diagnostic opportunities are increased and treatment is initiated closer to the time of admission to improve patient outcomes;
- The Indian ink technique for point-of-care laboratory screening is implemented and functional;
- The data can contribute information to MoH and provide opportunities for advocacy so that less expensive cryptococcosis diagnostic strategies are prioritized, maximizing the control and prevention of this neglected disease that, together with HIV, is devastating health and resources. socioeconomic in the country.
  1. Dissemination of results

The results will be presented first at the data collection sites (hospitals), then in the PhD program, at scientific conferences and finally published in scientific journals.

# Study Timeline

| **ACTIVITIES** | **MONTHS /2022 – 2026** | | | | | | | | | | | |
| --- | --- | --- | --- | --- | --- | --- | --- | --- | --- | --- | --- | --- |
|  | **02/2022** | **03-07/2022** | **08-12/2022** | **01-03/2023** | **04-12/2023** | **01/2024-03/2024** | **04/2024-12/2024** | **01-06/2025** | **07-09/2025** | **10/2025-11/2025** | **12/2025-03/2026** | **04/2026** |
| Literature review |  |  |  |  |  |  |  |  |  |  |  |  |
| Protocol preparation |  |  |  |  |  |  |  |  |  |  |  |  |
| Project Submission to the Doctoral Program |  |  |  |  |  |  |  |  |  |  |  |  |
| Defense of the research project |  |  |  |  |  |  |  |  |  |  |  |  |
| Submission of the Project to the Institutional Committee of Bioethics in Health of FM & MCH and CNBS |  |  |  |  |  |  |  |  |  |  |  |  |
| Assessment of the current situation (Pre-implementation phase) |  |  |  |  |  |  |  |  |  |  |  |  |
| Adaptation and implementation phase of the intervention |  |  |  |  |  |  |  |  |  |  |  |  |
| Manuscript Submission I |  |  |  |  |  |  |  |  |  |  |  |  |
| English and Ethics |  |  |  |  |  |  |  |  |  |  |  |  |
| Implementation Evaluation Phase and Manuscript Submission II |  |  |  |  |  |  |  |  |  |  |  |  |
| Manuscript Submission III |  |  |  |  |  |  |  |  |  |  |  |  |
| Specialty course and preparation of the financing proposal |  |  |  |  |  |  |  |  |  |  |  |  |
| Writing sabbatical |  |  |  |  |  |  |  |  |  |  |  |  |
| Thesis defense |  |  |  |  |  |  |  |  |  |  |  |  |

# Budget

| **Item** | **Amount** | **Unit cost (Mt)** | **Total (Mt)** |
| --- | --- | --- | --- |
| **Office Supplies** | | | |
| Pencil | 40 | 20,00 | 800,00 |
| Rubber | 40 | 20,00 | 800,00 |
| Pencil spinner | 40 | 20,00 | 800,00 |
| Pen | 40 | 25,00 | 1.000,00 |
| Ream of paper | 25 | 400,00 | 10.000,00 |
| Print |  |  | 30.000,00 |
| Copy |  |  | 22.000,00 |
| Recorder | 1 |  |  |
| **Subtotal 1** | | | **65.400,00** |
|  | | | |
| **Laboratory Material** | | | |
| India ink (30ml) | 6kits | 400,00 | 1.600,00 |
| Microscopic slides | 12cx | 975,00 | 11.700,00 |
| Lamellae | 12cx | 1410,00 | 16.920,00 |
| Gloves |  |  | 20.550,00 |
| **Subtotal 2** | | | **50.770,00** |
|  | | | |
| **Support Staff** | | | |
| Health professionals | 6 | 20.000,00 | 120.000,00 |
| **Subtotal 3** | | | **120.000,00** |
|  | | | |
| **Travel and communication** | | | |
| Travel and communication | | | 80.000,00 |
| **Subtotal 4** | | | **80.000,00** |
|  | | | |
| **Total** | | | **316.170,00** |
| **Unforeseen 10%** | | | **31.617.00** |
| **Total with 10% of unforeseen events** | | | **347.787.00** |

# APPENDICES AND ANNEXES

**Anexo I Versão 04, Outubro 2023**

**QUESTIONÁRIO**

(Clínicos e Técnicos de Laboratório)

**Implementação da técnica de tinta da China em urina para triagem laboratorial *point-of-care* da Criptococose em pacientes adultos infectados por HIV no sul de Moçambique.**

1. **INFORMAÇÃO DEMOGRÁFICA**

| **N^0^** | **Informação Demográfica** | **Resposta** |
| --- | --- | --- |
| 01 | Código do participante | ___ ___ ___/_______/_____/2023 |
| 02. | Unidade Sanitária: | 🞏HCM 🞏HGM 🞏HGJM 🞏 HPM 🞏HPX 🞏HCC |
| 03. | Idade | <30  ≥30  <40  ≥40 |
| 04. | Sexo | 🞏 Masculino 🞏Feminino |
| 05 | Nacionalidade | 🞏Moçambicana  🞏Estrageira |
| 06. | Qual é a sua principal área de trabalho ou unidade no hospital? (Por favor, marque UMA resposta) | 🞏 Medicina  🞏 Laboratório  🞏 Outra (por favor especifique:____________ |
| 07. | Qual é o seu nível de instrução? | 🞏 Médico internista  🞏 Residente em pós-graduação  🞏 Médico generalista  🞏 Enfermeiro Superior  🞏 Enfermeiro médio  🞏 Técnico de Laboratório  🞏 Outro (por favor especifique): ________ |
| 08. | Anos de prática | 🞏< 1 🞏 ≥1 🞏<5 🞏≥5 |

**Anexo II**  **Versão 04, Outubro 2023**

**QUESTIONÁRIO**

**Código ___ ___ ___/_______/_____/202___**

(RESPONSÁVEL DO LABORATÓRIO E TÉCNICOS**)**

**B/F**

**Implementação da técnica de tinta da China em urina para triagem laboratorial *point-of-care* da Criptococose em pacientes adultos infectados por HIV no sul de Moçambique.**

**ANÁLISE DA SITUAÇÃO ACTUAL**

| Código da US/LAB______ | Nível_____ | N^o^ de técnicos______ |
| --- | --- | --- |

1. **Com que frequência é efectuado o controlo de qualidade**

Sempre As vezes**** Nunca Não sei ****

1. **Indique o equipamento e material existente no seu laboratório**

Incubador  Cabine de biossegurança  Centrifuga  Microscópio  Lâminas microscópicas  Lamelas  Geleira 

1. **Qual é a condição da infraestrutura?**

Adequado  Inadequado 

1. **Com que frequência o laboratório tem material/equipamento para teste de criptococose?**

Sempre As vezes**** Nunca Não sei ****

1. **Com que frequência o laboratório tem reagentes para teste de criptococose?**

Sempre As vezes**** Nunca Não sei ****

1. **Estima o número de amostras para o diagnóstico da criptococose que são processadas por semana no seu laboratório**

<10 10 -- 20 ≥30

1. **Com que frequência em amostras suspeitos, é diagnosticado *Criptococcus* spp no seu laboratório?**

 100%  80 – 99% 50 – 79%  <50%

1. **Considera a criptococose uma doença negligenciada em Moçambique?**

Sim Não  Não sei 

1. **Seu laboratório sofre atrasos na emissão resultados ou interrompe o processamento das amostras devido à falta de reagentes?**

Sim  Não  Não sei 

1. **Você sente que a qualidade do trabalho é consistente em todos os turnos? (horário de trabalho, fim de semana, feriado, plantão noturno)**

Sim Não

1. **Se NÃO, na sua opinião em qual turno a qualidade do serviço do laboratório é comprometida?**

Horário de trabalho Fim de semana Feriado Plantão noturno

1. **Com que frequência você recebe treinamento em microscopia?**

1 treino/ano 2 treinos/ano nunca fui treinado

1. **Quando foi o seu último treino?**

>6 meses  ≥1 ano  ≥2 anos

1. **Indique por favor o seu nível de instrução**

Médico especialista  Médico generalista  Enfermeiro Técnico de Laboratório

1. **No laboratório existe base de dados eletrónico e funcional?**

Sim  Não  Não sei 

1. **Existe no laboratório livro de registo de dados?**

Sim  Não  Não sei ****

1. **O laboratório tem critérios para rejeição de amostras**

Sim  Não **** Não sei ****

1. **Que tipo de amostras são processadas no laboratório?**

Sangue Urina LCR Expetoração Biopsia

Outras (por favor especifique)_____________________________

1. **Com que frequência tem o EPI disponível (luvas) para manuseamento das amostras?**

Sempre As vezes Nunca Não sei 

1. **Que tipo de exames estão disponíveis no laboratório para diagnóstico de criptococose**

Tinta da China  CrAg  Cultura  Teste de aglutinação em latex (TAL) Ensaio imune enzimático (EIE) PCR

1. **Que microrganismos de origem fúngica são pesquisados no Laboratório**

*Criptococcus spp Candida spp Aspergillus spp Pneumocistes jirovecii*  Outros (por favor especifique)____________________

1. **O laboratório tem procedimentos operacionais padrão (POPs) de diagnóstico?**

Sim Não

1. **Qual é o tempo de resposta do Laboratório** (forneça sua melhor estimativa)

____min _____ horas

1. **Com que frequência são discutidos internamente os resultados dos pacientes antes de partilha com os clínicos?**

Sempre As vezes Nunca Não sei 

1. **Indique a forma de partilha de resultados com clínicos (**pode escolher mais do que uma resposta)

WhatsApp Email  Plataforma (*website*)  Agente de serviço faz chegar ao clínico Outra (por favor especifique)___________________

1. **Seu laboratório autoclava/incinera amostras, culturas ou material infecioso antes de descartar?**

Sim Não Não sei

1. **Fornecimento de água corrente no seu laboratório**

<12h/dia 12 - 16h/dia 24h/dia

1. **Fornecimento de energia no seu laboratório**

<12h/dia 12 - 16h/dia 24h/dia

1. **Tem alternativa de fornecimento de energia (gerador)?**

Sim Não

1. **Que outros desafios/dificuldades você encontra para efectuar um exame de *Cryptococcus?***

**Obrigado pela colaboração.**

**Anexo III**  **Versão 04, Outubro 2023**

**GUIÃO DE ENTREVISTA AO CLÍNICO**

**Código ___ ___ ___/_______/_____/202___**

**Implementação da técnica de tinta da China em urina para triagem laboratorial *point-of-care* da Criptococose em pacientes adultos infectados por HIV no sul de Moçambique.**

**DIAGNÓSTICO CLÍNICO-LABORATORIAL E *FEEDBACK* DO LAB**

1. Encontra muitos casos de criptococose enquanto cuidas de pacientes no seu consultório?
2. Você se sente habilitado o suficiente para cuidar de pacientes com doença criptocócica?
3. Você se sente a vontade para cuidar de pacientes com doença criptocócica?
4. Que sinais e sintomas seus pacientes com doença criptocócica costumam apresentar?
5. Quais doenças imitam ou se parecem com a doença criptocócica no seu consultório?
6. Que tipo de teste habitualmente solicita quando suspeita uma doença criptocócica?
7. Na sua opinião o pessoal do laboratório está disponível quando você tenta contatá-los?
8. A punção lombar está sempre disponível na sua US?
9. Que desafios você encontra se tiver que referir pacientes para punção lombar com o outro médico?
10. Em que se apoia para o diagnóstico da criptococose na sua Unidade Sanitária?
11. Tem alguns critérios para decidir por um tratamento seja sindrómico em vez do direcionado?
12. Considera complexo ou simples o fluxo de atendimento incluindo diagnóstico laboratorial e tratamento?
13. O que constitui barreira no fluxo de atendimento, diagnóstico laboratorial e tratamento de pacientes suspeito da criptococose?
14. Na sua opinião, que aspectos podem facilitar a aderência ao novo teste de diagnóstico laboratorial da criptococose na sua US/LAB
15. Tendo em conta as dificuldades que motivações encontras no âmbito de atendimento e tratamento de pacientes suspeitos de criptococose?
16. Em que frequência as suas decisões terapêuticas foram suportados por Laboratório?
17. Estima o tempo de resposta Laboratorial para disponibilidade do resultado.

**Obrigado pela colaboração.**

**Anexo IV.**  **Versão 03, Setembro 2023**

**QUESTIONÁRIO**

**Código ___ ___ ___/_______/_____/202___**

**Implementação da técnica de tinta da China em urina para triagem laboratorial point-of-care da Criptococose em pacientes adultos infectados por HIV no sul de Moçambique**

**(Práticas/conduta _Clínico)**

1. **Indique o principal método de diagnóstico de criptococoses em uso no seu laboratório**

Clinico ; Tinta da China ; CrAg ; Cultura ; Teste de aglutinação em latex (TAL) ; Ensaio imune enzimático (EIE); PCR

1. **Com que frequência solicitas o teste?**

Sempre As vezes**** Nunca Não sei ****

1. **Com que frequência o teste de *Criptococcus* esta disponível?**

Sempre As vezes**** Nunca Não sei ****

1. **Tempo de resposta do Laboratório** (forneça sua melhor estimativa)

______min _______horas

1. **Tempo de início de tratamento após o resultado positivo** (forneça sua melhor estimativa)

______horas ______dias

1. **Considera a criptococose uma doença negligenciada em Moçambique?**

Sim Não 

1. **Antes de solicitar o teste que factores considera? (**pode escolher mais do que uma resposta)

**** Gravidade da doença

 Carga do trabalho na clínica/laboratório

 Idade do Paciente

 Disponibilidade de serviços de laboratório

CD4<100cell/mm^3^

CD4<100cell/mm^3^

 Outro (Faz favor mencionar):____________________________________________

1. **Qual é a sua opinião sobre o formulário de solicitação dos enxames laboratoriais?**

Adequado  Inadequado 

1. **O laboratório notifica as enfermarias quando há introdução de um novo exame incluindo os seus parâmetros?**

Sim Não

1. **O laboratório notifica imediatamente os resultados críticos**

Sim Não

1. **Com que frequência o laboratório avisa a você quando há interrupção de um determinado exame?**

Sempre As vezes Nunca Não sei 

1. **Você sente que a qualidade do trabalho é consistente em todos os turnos? (horário de trabalho, fim de semana, feriado, plantão noturno)**

Sim Não

1. **Se NÃO, na sua opinião em qual turno a qualidade do serviço é comprometida?**

Horário de trabalho Fim de semana Feriado Plantão noturno

1. **Quantos pacientes assiste por semana? (forneça sua melhor estimativa)**

<10 10 - 20 ≥30

1. **Qual é o perfil do paciente que chega á US**

Crítico moderado

1. **Assinale os sinais/sintomas da criptococose que observas nos seus pacientes**

cefaleia febre rigidez da nuca convulsões acne

Outro (por favor mencione):__________________________

1. **Existem critérios para triagem?**

Sim  Não 

1. **Guião de definição de caso disponível**

Sim  Não 

1. **O rastreio de criptococose em pacientes HIV faz parte da rotina na sua US?**

Sim  Não 

1. **O que constitui barreira para o diagnóstico e tratamento de pacientes suspeito da criptococose? (**pode escolher mais do que uma resposta)

 Baixa auto-confiança motivado por sobrecarga do trabalho no Laboratório

 Rotura de reagentes

 Rotura do teste

 Dificuldades para obtenção da amostra

Outro (Faz favor mencionar):_____________________________________________

1. **Com que frequência você confia completamente os resultados do teste do paciente**

 100%  80 – 99% 50 – 79%  <50%

1. **Quais factores podem fazer com que você trate criptococose na presença de um resultado** **negativo do teste?**

 Forte suspeita clínica

 O resultado do teste pode ser indeterminado, incorrecto ou inconsistente

 Idade do paciente

 Preferência

 Outro (Faz favor mencionar):____________________________________________

1. **O pessoal do laboratório está disponível quando você tenta contatá-los?**

Sim  Não 

1. **Na sua opinião o laboratório disponibiliza a segunda via do resultado quando você solicita?**

Sim  Não **** Nem sempre

1. **Anfotericina B esta geralmente disponível na Unidade sanitária?**

Sim  Não ** **Não sei Nem sempre

1. **Os pacientes podem adquirir fluconazol gratuitamente na Unidade sanitária?**

Sim  Não ** **Não sei

1. **Há registo de seguimento dos pacientes com resultados positivos para Criptococose**

 Sim

Não, os pacientes não retornam depois da primeira visita

1. **No livro tem informações detalhado de contacto dos pacientes positivos para *Criptococcus*?**

Sim  Não **** Não sei 

1. **Se for solicitado para melhorar algo no diagnóstico e tratamento da criptococose que alterações sugeria?**

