**Quantitative data analysis**

Quantitative data will be analyzed using the R studio statistical package. Univariate descriptive analyses will be carried out (mean or median age, standard deviation and variance will be calculated), percentage frequencies of the following variables: tests requested, doctors/laboratory technicians who adhered to the intervention, chi-square to check for associations between the intervention/test and the variables (level of education of the professional, availability of the test, severity of the disease and gender) and logistic regression to estimate the relationship between adherence to the test and factors severity of the disease, work overload in the US/laboratory, level of education of the professional, shift, gender, availability of laboratory services.

A Likert scale will be used to assess the level of satisfaction of all those involved in the intervention (doctors and laboratory technicians) during the study period. And the frequencies of the information obtained will be calculated.

The results will be described and presented in tables and graphs using the Microsoft Excel program. A p-value of <0.05 will be considered significant.

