# Practices and challenges in the laboratory diagnosis of cryptococcosis in six hospitals in the three southern provinces of Mozambique.

This is a cross-sectional study with a mixed approach. The qualitative approach will be generic, where the current situation will be assessed before the intervention is implemented (Figure 2: Pre-implementation phase) in order to identify elements of the social, health, administrative, and structural context that may or may not favor the intervention in the local context.

The assessment of the current situation will be carried out in six hospitals (MCH, MGH, JMGH, MPH, XPH, and CHC) over three months. Sampling will be non-probabilistic, and intentional with regard to the participants and by convenience with regard to the study sites.

The data for this study will be obtained through semi-structured questionnaires (Annexes I, II, and IV) and interviews (Annex III) with health professionals from each hospital (clinicians from the medical service and microbiology laboratory technicians); and a list will be made of the equipment, existing material and a description of the cryptococcosis diagnoses currently carried out in each hospital involved in the study and to identify barriers and facilitators to implementing the technique of diagnosing cryptococcosis with urine samples.

The data will be analyzed using the R studio statistical package, where the following analyses will be carried out: descriptive analysis (calculating frequencies, mean or median, standard deviation, and variance); and chi-square to compare frequencies. The results will be described and presented in tables and graphs. A p-value of <0.05 will be considered significant.

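### One barrier box in the Annex IV clinician questionnaire merges low self-confidence with laboratory overload, so the closed options cannot give a separate frequency for either

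*Protocol*

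**What the plan says.** Annex IV (clinician practices and conduct) contains a multiple-response item that asks "O que constitui barreira para o diagnóstico e tratamento de pacientes suspeito da criptococose". It has four closed options and an *Outro* line for free text. Three options each name a single barrier: reagent stock-out, test stock-out, and "Dificuldades para obtenção da amostra" (difficulty in obtaining the sample). The remaining option is "Baixa auto-confiança motivado por sobrecarga do trabalho no Laboratório".

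The baseline assessment (section 7.9, first sub-study) uses this annex with the other baseline instruments, among other things "to identify barriers and facilitators to implementing the technique of diagnosing cryptococcosis with urine samples". The same sub-study plans descriptive frequencies and chi-square comparisons of the questionnaire data.

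Workload also appears elsewhere. Another Annex IV item, on what the clinician weighs before requesting a test, offers "Carga do trabalho na clínica/laboratório". The Quantitative data analysis section lists "work overload in the US/laboratory" as a factor in a logistic regression for adherence to the test. The Annex III interview guide asks clinicians "Você se sente habilitado o suficiente para cuidar de pacientes com doença criptocócica" and, as an open question, "O que constitui barreira no fluxo de atendimento, diagnóstico laboratorial e tratamento de pacientes suspeito da criptococose".

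**The concern.** The option is double-barrelled: one tick stands for two constructs and for a causal claim linking them. It also leaves open whose confidence is meant, the responding clinician's or the laboratory's. Several clinicians have no closed option that fits: one who sees overload without loss of confidence, one who lacks confidence for another reason, and one who sees both but does not think the first causes the second.

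The two barriers call for different responses. The conceptual framework in section 6 treats training and workflow adaptation as separate kinds of support. A baseline report that could say how many clinicians named each barrier would be more useful than one that can only report the merged box. No later analysis can divide a merged tick.

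**Working it through.** The protocol states no figure that rests on this item, so there is none to reproduce. The check has two parts.

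**1. Does another closed item supply the missing counts?**

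| Construct | Where else it is asked | Does it give a closed count as a barrier? |
| --- | --- | --- |
| Laboratory overload | Annex IV, factors weighed before requesting a test | No. It is a factor in test requesting, and it merges clinic and laboratory |
| Clinician self-confidence | Annex III, skill and ease questions | No. These are interview questions, so the data are qualitative |
| Trust in the test result | Annex IV, later item | No. This is a different construct |
| Technician confidence with the urine test | Annex V, laboratory version | No. Different respondents, after the intervention |
| Any barrier | Annex III open question; closing open questions of Annexes II and IV; *Outro* | No. Free text or qualitative data |

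The Annex IV item is the only closed list of barriers in the annexes. Neither construct can be counted separately from its tick-boxes.

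**2. How wide is the uncertainty?**

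Input: the clinicians listed by hospital in section 7.5 number 8 + 4 + 4 + 3 + 3 + 2 = 24. Assumption: all 24 complete Annex IV. One tick is then 1/24 = 4.2 percentage points.

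Let *k* clinicians tick the merged box, and ignore *Outro* for the moment.

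- **Literal reading** (tick only if both hold and are causally linked). All *k* hold both barriers. The other 24 − *k* may still hold either one. Each barrier's count lies between *k* and 24.
- **Loose reading** (tick if either holds). The 24 − *k* non-tickers hold neither. Among the *k*, each barrier's count lies between 0 and *k*, with the two counts summing to at least *k*.

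Take *k* = 12 as an illustration; the protocol gives no expected value. The literal reading gives 12 to 24 clinicians per barrier (50% to 100%). The loose reading gives 0 to 12 (0% to 50%). The data do not show which reading a respondent used. Entries under *Outro* narrow these ranges only as far as respondents volunteer them.

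**The case against.** The strongest reply is that little depends on this box, and much of that reply stands.

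- **No one is forced into a false answer.** A reader might infer that a clinician must tick something untrue or stay silent. The *Outro* line lets either barrier be written in alone. However, unprompted free text is not comparable with ticked boxes, so the loss of a clean count remains.
- **The adaptation phase does not hang on this item.** A reader might infer that the study will be unable to tell a training need from a workflow need. The protocol does not support that. Annex III asks separately about skill, ease, care flow and barriers, and Annex II asks technicians about microscopy training. Section 7.9 (second sub-study) provides both training and an information-sharing workflow, and section 8 involves all clinicians and technicians in the training. None of this is made conditional on the box.
- **The regressions are not shown to suffer.** A reader might infer that the overload covariate is compromised. Its wording closely matches the separate workload box among the factors weighed before requesting a test, and nothing says the barrier item supplies it. No specific test or model on the barrier box is planned, and barriers are not in the variable list for the first objective.
- **The link to the urine technique is loose.** The item asks about barriers to diagnosis and treatment in general, whereas the quoted aim of the first sub-study concerns implementing the urine test. The item still serves that sub-study's broader subject of practices and challenges in diagnosis.
- **Separating clinic from laboratory overload is not required.** The analysis plan carries workload as one combined variable, so a clinic box is a refinement only.

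A truthful tick, read literally, does endorse both parts. That resolves the tickers but leaves the non-tickers unknown, and it depends on all respondents reading the option that way.

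**Conclusion.** The point holds as a minor flaw in instrument wording. The option is double-barrelled with a built-in cause, and the closed options of the only closed barrier list cannot give a separate frequency for low self-confidence or for laboratory overload. Among 24 clinicians the resulting ambiguity can span much of the scale, assuming all of them answer and few use *Outro*. The distinction survives only in free text and interviews. No consequence is shown for the stepped-wedge design, the content of the adaptation phase or the specified regressions. What is lost is a descriptive baseline result.

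**What to change.** Before baseline collection, replace the merged option in Annex IV with two boxes: *low self-confidence* (stating whose) and *work overload in the laboratory*. A third box, *work overload in the clinic*, is optional. Remove the causal wording. Multiple answers are already allowed, so a clinician who sees both can tick both, and the REDCap form needs only one or two extra tick-boxes.

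If responses have already been collected with the merged box, report it under its literal wording as one combined category. Take any separate statement about confidence or overload as a barrier from the *Outro* text and the interviews, labelled as such.
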